### Neighborhood soundscapes

Positive and negative auditory exposures will be assessed by acoustic recordings collected by 90 AudioMoth v1.1.0 acoustic loggers (Open Acoustic Devices). Nine devices will be placed at least 100 m apart randomly in a 500 m grid around each park, and one device will be placed inside each park. We will record for one week in June, corresponding with Audubon’s bird surveys, selecting days to standardize weather conditions. To predict negative auditory exposure, we will calculate environmental noise metrics known to relate to human annoyance, health, and perception including: L_Aeq,T_ (A-weighted equivalent sound level (L) over time); L_Amax_ (maximum A-weighted equivalent L over time); L_A10_ and L_A90_ (A-weighted L exceeded 10 and 90% of time); L_A10_ - LA_90_, LDN (Day-Night average L, where night events receive a 10 dB penalty); L_DEN_ (Day-Evening-High equivalency L); roughness (temporal variation in amplitude), and sharpness [125–128].

To examine positive auditory exposure, trained staff will count the number and duration of sound categories using observations of spectrograms in Raven Pro software (Cornell University, Ithaca, NY). Sound categories are ‘anthropogenic’ (e.g., vehicle, people), ‘geological’ (e.g., wind), and ‘biological’ (e.g., birdsong). Additionally, we will further categorize bird song to species, in order to generate species richness and diversity of the acoustic community [129]. We will combine the duration/frequency and richness of biological with geological sounds into a metric of positive exposure [130]. Using values of each acoustic exposure metric, we will then predict levels throughout the study area using spatial kriging models [131]. We will extract the positive and negative exposure levels for participants at each time point.

### Weather data

While we restrict data collection to summer months (May–September), weather conditions at the time of data collection and the two weeks prior to data collection may influence both exposures of interest and outcomes. Thus, we will compile daily precipitation and high temperature data for every day during data collection and the two weeks preceding data collection for each time point, from the weather station at Detroit airport (DTW) [132, 133].

### Statistical analysis

Assuming a longitudinal panel design, we will compare INT to CNT at baseline using as appropriate ANOVA-F-tests, chi-square tests and non-parametric tests to determine equivalence of potentially confounding physiological and contextual participant characteristics. If substantive differences are found, they will be controlled for in subsequent analyses by regression techniques, guided by the degree of dissimilarity [134]. Equivalence between groups will be assessed on age, sex, ethnicity, employment status, length of residence, marital status, attitudes towards nature, perceived safety, and pre-existing health conditions. We will calculate descriptive statistics for all variables at baseline and each post-restoration time point. Likewise, park characteristics will be summarized for the INT and CNT parks for each time point.

We adopt a regression-based approach to multivariable modeling that addresses features of clustering of participants within parks and correlation over time in repeated assessments. Repeated measures ANOVA, or more apropos, generalized linear (mixed) models (GLMM) will be used [135–137]. Denote by $$ {\mathit{\mathsf{Y}}}_{\mathit{\mathsf{it}}} $$ an outcome in the *i*-th participant in the *h-*th park assessed at time *t*. It is assumed that an individual is primarily exposed to one park. Generally, outcomes are assessed at baseline and at least 3 additional time-points, denoted t = 0, 1, 2, 3. Our hypotheses concern the expected response: $$ {\textsf{g}}\left({\mu}_{{\textsf{hi}\textsf{t}}}\right)={\mathbf{\textsf{x}}}_{{\textsf{it}}}^{\prime}\beta +\mathbf{\textsf{z}}{\hbox{'}}_{{\textsf{ht}}}{\mathbf{\textsf{b}}}_{{\textsf{hi}}} $$ .The GLMM is expressed as $$ {\textsf{g}}\left({\mu}_{{\textsf{hi}\textsf{t}}}\right)={\mathbf{\textsf{x}}}_{{\textsf{it}}}^{\prime}\beta +\mathbf{\textsf{z}}{\hbox{'}}_{{\textsf{ht}}}{\mathbf{\textsf{b}}}_{{\textsf{hi}}} $$ with link function *g* appropriate to type of outcome (continuous, categorical, count, ordinal) random effects $$ {\mathbf{\textsf{b}}}_{{\textsf{hi}}} $$ to capture serial correlation within participant measures and clustering [138]. The covariates $$ {\mathbf{\textsf{x}}}_{{\textsf{hit}}} $$ are participant characteristics, some of which are time-invariant such as the aforementioned sociodemographic variables; $$ {\mathbf{\textsf{z}}}_{{\textsf{ht}}} $$ are characteristics of park *h* at time *t.* Minimally, the predictor variables are: a single indicator for GROUP, with CNT as referent, three indicators for TIME, corresponding to t = 1, 2, 3 with baseline t = 0 as referent, and GROUP×TIME interactions. A measure of exposure to environmental stimuli is included in participant characteristics. The GLMM allows us to formulate and test hypotheses on functions of the regression parameters β, including: i) point-in-time comparison between INT and CNT, e.g., at each follow-up year; ii) time-averaged comparison between INT and CNT; iii) within group comparison for change over time; and iv) change in INT compared to the corresponding change in CNT via DID. SAS Software v9.4 (Analytics 15.1 or higher) will be used for statistical analyses.

To address missingness in our response data, we will employ strategies for imputation [139]. The techniques described above allow missing at random (MAR). Inverse probability weighting [140] will be investigated to accommodate missing data patterns that are not MAR. To minimize bias in analysis, we will adjust for factors that may be unbalanced between groups and examine the robustness of our conclusions under deviations of model assumptions. Below, we outline specific analyses for each hypothesis to be tested.

#### Hypothesis 1

We will separately evaluate average activity counts/minute and average moderate-to-vigorous minutes over the one-week observation period for each of the data collection periods. The predictor of interest is binary: INT versus CNT.

#### Hypothesis 2

The primary outcome, ‘green PA’, will be average activity counts/minute and average moderate-to-vigorous minutes over the one-week observation period while in parks and greenspaces in Detroit, as a subset of all activity.

#### Hypothesis 3

We hypothesize there will be an association between PA and the visual and auditory exposures. Instead of a binary predictor of interest, we will use continuous predictors for visual and auditory park exposures. Interaction terms between positive and negative exposures will also be assessed, as evidence suggests that negative sounds deplete the restorative benefits of natural sounds, [141] and that parks are often dominated by noise [45, 142].

#### Hypothesis 4

Each stress outcome will be evaluated separately and treated continuously. We will also explore potential mediators (e.g., PA) by adding each to mixed models as fixed terms, and adjusted mediation and partial correlation coefficients explored. We will adjust for prescription medication history and symptoms of acute illness as potential confounders.

#### Hypothesis 5

We will assess relationships with each stress indicator, in turn.

#### Hypothesis 6

We hypothesize there will be an association between each stress indicator and these exposures.

#### Hypothesis 7

We will compare INT and CNT groups from baseline through three-years post-restoration for changes in CRP and A1C (continuously measured) between INT and CNT groups. We will also consider the inclusion of prescription medication history and symptoms of acute illness as potential confounders.

#### Hypothesis 8

We will compare INT and CNT groups from baseline through three-years post-restoration for changes in blood pressure, hip-to-waist ratio and BMI (continuously measured) between INT and CNT groups.

Despite our best effort to recruit and retain a longitudinal panel of participants, we may face problems with attrition higher than the projected attrition rates of 15% at t = 1, another 10% at t = 2, and 5% at t = 3. With these levels, our longitudinal panel becomes unbalanced but valid inference can be made under the assumption that attrition is at random (MAR). We describe another strategy, *repeated cross-sections*.

By repeated cross-sections we mean a series of independent samples are drawn at the subsequent times t = 1, 2, 3 following the initial baseline sample at t = 0. It could happen that a participant in the baseline sample is also in any of the subsequent samples, but this is at random. With repeated cross-sectional samples, we cannot estimate *within participant* change in outcomes, which is the key advantage of the longitudinal panel approach. However, we can still assess patterns of change at an aggregate level as explained in the following text.

Consider an outcome $$ {\mathit{\mathsf{Y}}}_{\mathit{\mathsf{it}}} $$ at time *t* in the *i-*th participant, and the linear model $$ {{\textsf{Y}}}_{{\textsf{i}\textsf{t}}}={\mathbf{\textsf{x}}}_{{\textsf{i}\textsf{t}}}^{\prime}\beta +{\alpha}_{{\textsf{i}}}+{\varepsilon}_{{\textsf{i}\textsf{t}}} $$ with exogenous covariates $$ {\mathbf{\textsf{x}}}_{{\textsf{it}}} $$, *t* = 0, 1, 2, 3. We aggregate each sample into *C* cohorts defined as participants who share common characteristics such as age, sex, neighborhood park, etc. Aggregation of participants to the cohort level *c* replaces the model by the cohort model $$ {\overline{{\textsf{Y}}}}_{{\textsf{c}\textsf{t}}}={\overline{{\mathbf{\textsf{x}}}^{\prime}}}_{{\textsf{c}\textsf{t}}}\beta +{\overline{\alpha}}_{{\textsf{c}}}+{\overline{\varepsilon}}_{{\textsf{c}\textsf{t}}} $$, *c* = 1, …,*C*, *t* = 0, 1, 2, 3. (Bar notation refers to averages over participants within cohort/time). Our observed data become a pseudo-panel of repeated observations on cohorts over time, and estimation of differences between INT and CNT cohorts could be compared over time, although the cohorts are not comprised of the same participants from one time point to the other. Some technical issues will need to be addressed to ensure a consistent estimator of *β* [143–146].

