### Sample size

Assuming a longitudinal panel design, sample size assessments for the study are based on achieving 82% power to test the hypotheses. The effect measure is a difference-in-differences (DID) — in hypotheses 1–3, i.e., the expected change in PA from baseline to three-years post-restoration in INT parks compared to the corresponding change in CNT parks. Hypotheses 3–6 concern a DID in stress outcomes. A review of the literature on PA [46] and cortisol [47] suggests an effect size (EF) of 0.35 could be posited. Accordingly, we calculate our sample size requirements to detect an EF of 0.35 or better with 82% power. Two other design features are: a serial correlation *r* between repeated measures over time and intra-class correlation (ICC) *ρ* for clustering within neighborhood parks. In community-intervention studies such as ours, *ρ* is small [48–51]. Plausible values from the literature and our own experiences, suggest *r* ≥ 0.35 and *ρ ≤* 0.004. With a total of nine parks (4 INT, 5 CNT), we will need a sample of 450 participants, or 50 per park, to detect EF = 0.35 with 82% power, based on a two-sided test at significance level 5%. Because attrition is expected over the study period, we will recruit a total of 620 participants at t = 0 (baseline) to account for attrition of 15% at t = 1 and another 10% at t = 2 and 5% at t = 3. Our sample size assessment may also be deemed conservative as it does not account for potential influence of fixed covariates, which should increase precision on the intervention effect estimate by reducing residual variance resulting in a positive effect on power.

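### In the panel difference-in-differences, main-effect adjustment for time-invariant characteristics cannot correct differing trends and adds essentially no precision, so the "conservative" sample-size remark is unsupported there

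*Protocol article*

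**What the plan says.** The Sample size section defines the effect measure as a DID, for physical activity "the expected change in PA from baseline to three-years post-restoration in INT parks compared to the corresponding change in CNT parks", under a longitudinal panel design. It adds that the calculation may be regarded as conservative because "it does not account for potential influence of fixed covariates, which should increase precision on the intervention effect estimate", the stated mechanism being a smaller residual variance.

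The Statistical analysis section compares INT with CNT at baseline by ANOVA F, chi-square and non-parametric tests, whose stated purpose is to determine equivalence. It lists nine characteristics: age, sex, ethnicity, employment, length of residence, marital status, attitudes to nature, perceived safety and existing health conditions. Then: "If substantive differences are found, they will be controlled for in subsequent analyses by regression techniques", guided by how dissimilar the groups are.

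The mixed model contains, as a minimum, GROUP, three TIME indicators and GROUP×TIME. Its covariates "are participant characteristics, some of which are time-invariant such as the aforementioned sociodemographic variables". No covariate×TIME term is named. The DID is one of four contrasts listed.

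**The concern.** Park neighborhoods are not randomized, so the DID depends on the two groups having the same trend in the absence of restoration. A characteristic threatens it when it is unevenly distributed and also predicts a different change over time. A difference in level alone is already removed by differencing.

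The plan's adjustment step looks at level. Covariates enter because the groups differ at baseline, and the only time interaction named is with GROUP. If time-invariant characteristics enter as main effects, adjusted and unadjusted DIDs will agree almost by construction, and that agreement could be read as evidence against confounding.

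The selection rule is weak in its own right. A non-significant test of difference does not show equivalence, person-level tests ignore clustering in nine parks, and no threshold defines a substantive difference. The precision remark in the Sample size section credits fixed covariates with a margin that time-invariant ones do not supply for this effect measure.

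**Working it through.** **Inputs from the Sample size section.** Effect size 0.35 SD; two-sided 5%; 4 INT and 5 CNT parks of 50, so 200 and 250 people; the plausible values quoted "suggest *r* ≥ 0.35 and *ρ ≤* 0.004", used at their boundaries.

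**1. The stated power.** The protocol gives no formula, so two standard forms were tried.

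- Design-effect form: variance = 2(1−r)(1/200 + 1/250)[1 + 49ρ] = 1.3 × 0.009 × 1.196 = 0.01399. Standard error 0.1183; 0.35/0.1183 = 2.96; power = Φ(2.96 − 1.96) = 84.1%.
- Park-by-time form: variance = 1.3 × 0.009 + 2 × 0.004 × (1/4 + 1/5) = 0.0117 + 0.0036 = 0.0153; power 80.8%.

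The stated 82% lies between them. Retention also reproduces: 620 × 0.85 × 0.90 × 0.95 = 450.6.

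**2. Precision.** Let a time-invariant covariate explain a share R² of total variance (assumed; the protocol gives none). Adjustment changes σ² from 1 to 1−R², and r to (r−R²)/(1−R²). Then

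σ²(1−r) becomes (1−R²) − (r−R²) = 1−r = 0.65, whatever R² is.

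The covariate removes only between-person variance, which the within-person change had already removed. Holding the design effect at 1.196:

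| Assumed R² | Adjusted r | DID power | DID power if residual variance fell at fixed r | Point-in-time power |
|---|---|---|---|---|
| 0 | 0.350 | 84.1% | 84.1% | 92.1% |
| 0.1 | 0.278 | 84.1% | 87.7% | 94.5% |
| 0.2 | 0.187 | 84.1% | 91.1% | 96.5% |
| 0.3 | 0.071 | 84.1% | 94.3% | 98.1% |

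The fifth column shows the kind of contrast for which the protocol's reasoning does hold.

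**3. Bias.** In a complete panel with identity link and random intercept, GROUP×TIME is estimated from within-person changes, and a time-invariant main effect cancels from each of them. If the covariate differs between groups by d SD and shifts the three-year change by k per covariate SD, the DID is biased by d × k. For assumed d = 0.4 and k = 0.2 this is 0.08 SD, and 0.08/0.35 = 23%. Halving either input halves the bias to 0.04; if either is zero, there is none.

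Simulated mean DID, true effect 0, R² = 0.2, r = 0.35, no park effect (all but r assumed):

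| Setting | Unadjusted | Main effect | Covariate×TIME |
|---|---|---|---|
| Complete 450, d = 0.4, k = 0.2 (200 runs) | 0.079 | 0.079 | 0.001 |
| 620 recruited, 15/10/5% dropout at random, same d and k (200 runs) | 0.070 | 0.072 | −0.006 |
| Complete 450, d = 0.5, k = 0.2 (60 runs) | 0.094 | 0.094 | −0.001 |
| 620 recruited, covariate-related dropout in opposite directions by group, d = 0.5, k = 0 (60 runs) | −0.168 | −0.018 | −0.019 |
| Repeated cross-sections, INT composition shifting by 0.5 SD, k = 0 (60 runs) | 0.227 | 0.005 | 0.002 |

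Monte Carlo error is about 0.007 in the 200-run rows and about 0.014 to 0.017 in the others. In the complete panels, unadjusted and main-effect estimates agree to about 1e-14, with the same standard error (0.108). Under random dropout the main effect lowers the standard error only from 0.103 to 0.102 and leaves the trend bias. The last two rows show where main effects do remove bias.

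**The case against.** The strongest reply is that the protocol never says that covariates enter only as time-invariant main effects. The model terms are a stated minimum, only some covariates are called time-invariant, and a SAP could add interactions. This stands: the protocol does not rule out covariate×TIME terms, and their absence from the article is not itself the finding. The finding is that the selection rule it states is aimed at level imbalance, and that the precision argument it states does not fit its own effect measure.

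A reader might go further and infer that the planned adjustment removes no confounding. The documents do not support that. The protocol expects an unbalanced panel, has a repeated cross-section fallback, and lists point-in-time and time-averaged contrasts; main effects matter in all of these. Hypotheses 3, 5 and 6 concern associations with continuous predictors or activity levels, not a GROUP×TIME contrast. Medication history and acute illness are named for Hypothesis 4 without any baseline test, and the annual survey and the weather data can supply time-varying covariates. Selection is not purely by p-value either, since it refers to substantive differences and degree of dissimilarity. Matching of neighborhoods is a further safeguard.

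A reader might also infer that the conservative-power remark is simply false, or that the 82% is wrong. Neither follows. The remark is hedged, "fixed" may mean fixed-effect terms, and time-varying covariates can reduce within-person variance. The 82% does not depend on the remark.

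Finally, the imbalance and trend used to size the bias are assumptions. That also stands.

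**Conclusion.** The point holds in a limited form. For the panel DID behind the sample size, main-effect adjustment for time-invariant characteristics leaves the GROUP×TIME estimate and its standard error essentially unchanged, and so cannot correct trends that differ with those characteristics. This is exact for a complete panel with identity link and random intercept, and close to it under random dropout at the projected rates. Baseline tests of difference neither show equivalence nor identify the covariates that threaten a DID.

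For time-invariant covariates the conservative-power remark is unsupported: the gain in DID power is zero at any R², against the 3.6 to 10.2 percentage points that its reasoning would imply at assumed R² of 0.1 to 0.3 (87.7 − 84.1 and 94.3 − 84.1). The power figure itself is unaffected. The 0.08 SD bias is illustrative only, since the protocol supplies neither the imbalance nor the trend. This should be changed, but it does not invalidate the analysis.

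**What to change.** - Replace test-based selection with a short list fixed in advance from the nine characteristics, and report standardized differences descriptively.
- In the linear DID models, enter the baseline value of each listed covariate with covariate×TIME terms. Keep main-effect adjustment for the contrasts and designs where it works, and keep the named adjustment for medication and acute illness.
- Delete the sentence calling the sample size conservative, or limit it to contrasts or time-varying covariates for which it holds.

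The cost is wording and some parameters. In the simulations, one continuous covariate with its TIME interactions raised the standard error by 1.6% at an assumed 0.4 SD imbalance (0.1087 to 0.1104) and 3.0% at 0.5 SD (0.1082 to 0.1115). All nine would need at least 9 × 3 = 27 interaction terms, and more for multi-category variables, which is why the list should be short.

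### One set of random effects carries both serial correlation and park clustering; if these act as participant intercepts and correlation fades over the years, the standard error of the baseline-to-year-3 difference-in-differences is too small

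*Protocol article*

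**What the plan says.** The Statistical analysis section opens the modelling plan with "Repeated measures ANOVA, or more apropos, generalized linear (mixed) models (GLMM) will be used". It then gives the linear predictor as fixed effects x'β plus z'_ht b_hi. The b_hi are random effects "to capture serial correlation within participant measures and clustering". The z_ht "are characteristics of park" h at time t. The fixed part has group, three time indicators and their interaction. "Generally, outcomes are assessed at baseline and at least 3 additional time-points, denoted t = 0, 1, 2, 3".

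The Sample size section defines the effect for the physical activity hypotheses as "the expected change in PA from baseline to three-years post-restoration in INT parks compared to the corresponding change in CNT parks". Hypotheses 1, 2, 4, 7 and 8 all compare intervention with control at three years. The same section allows for "a serial correlation *r* between repeated measures over time" and says that plausible values "suggest *r* ≥ 0.35 and *ρ ≤* 0.004". It gives no values by length of interval.

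Two other places bear on the point. The Control description expects the control parks to stay in their present unmaintained state throughout. The Statistical analysis section also makes a general promise to check how robust the conclusions are to departures from the model assumptions. It names no check of the covariance.

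**The concern.** One set of random effects is asked to do two jobs: describe how a person's measurements correlate over four years, and describe clustering within parks. Its multiplier is a list of park features, which is not a natural description of either.

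Under the written form, the covariance between years s and t for one person is z'_hs D z_ht plus residual error when s = t, where D is the covariance matrix of the random effects. Where the park does not change, this is the same number for every pair of years, exactly as with a participant intercept. Where the park is restored, it follows the state of the park and not the time elapsed. In neither case is a person's correlation free to fall as the interval lengthens. Repeated measures ANOVA in its classical univariate form also pools the error over all visits.

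This matters because the contrast of interest spans the longest interval in the study. A constant-correlation model takes its residual variance from the average over all six pairs of visits, whereas the sampling variance of the year-3 change depends on the three-year correlation alone. If the latter is below the average, the interval is too narrow and the test rejects too often.

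**Working it through.** **Inputs from the article.** Four visits; 450 participants, 50 per park, in 4 intervention parks (200) and 5 control parks (250); effect size 0.35; two-sided 5%; power 82%; r = 0.35; ρ = 0.004; 620 recruited, with attrition of 15%, 10% and 5%.

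**The plan's own figure.**

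- Clustering inflation: 1 + 49 × 0.004 = 1.196.
- Variance of the DID, clustering applied as a multiplier: 2(1 − 0.35) × 1.196 × (1/200 + 1/250) = 1.5548 × 0.009 = 0.01399. SE 0.1183, power Φ(0.35/0.1183 − 1.96) = 84.1%.
- Variance with clustering added: [1.30 + 2 × 49 × 0.004] × 0.009 = 1.692 × 0.009 = 0.01523. SE 0.1234, power 81.0%.
- Attrition: 620 × 0.85 × 0.90 × 0.95 = 450.6.

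The stated 82% lies between the two variants. One r is enough here, because the calculation concerns one contrast over one interval.

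**Effect of holding the correlation constant.** Take unit variance at each visit, complete data, and correlations r1, r2, r3 at one, two and three years. Four visits give three one-year pairs, two two-year pairs and one three-year pair.

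- Average correlation: r̄ = (3r1 + 2r2 + r3)/6.
- The random-intercept model's variance of the year-3 DID is proportional to 2(1 − r̄).
- The true variance is proportional to 2(1 − r3).
- SE ratio (model to true) = √[(1 − r̄)/(1 − r3)].
- Actual two-sided error of the nominal 5% test = 2[1 − Φ(1.96 × ratio)].

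The article gives no values by interval. The patterns below are assumptions that keep its 0.35 at three years.

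| r1 / r2 / r3 | r̄ | SE ratio | Actual error |
|---|---|---|---|
| 0.35 / 0.35 / 0.35 | 0.350 | 1.000 | 5.0% |
| 0.45 / 0.40 / 0.35 | 2.50/6 = 0.417 | √(0.583/0.65) = 0.947 | 6.3% |
| 0.55 / 0.45 / 0.35 | 2.90/6 = 0.483 | √(0.517/0.65) = 0.892 | 8.1% |
| 0.65 / 0.50 / 0.35 | 3.30/6 = 0.550 | √(0.450/0.65) = 0.832 | 10.3% |

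**Check by simulation with the planned dropout.** This used 620 participants, 15/10/5% attrition, a random-intercept model fitted by REML, no park effect, and 2,500 data sets per pattern. In the order of the table, the SE ratios were 1.01, 0.96, 0.88 and 0.83, and the rejection rates were 4.6%, 6.3%, 8.1% and 10.2%. Dropout at the planned rates does not change the picture.

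**Another shape of decay.** First-order autoregressive correlation with r1 = 0.70 (three-year value 0.343) gives a ratio of 0.81 and an error of 11.3%; simulation with complete data gave 11.2%.

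**Other contrasts.** The bias is not always in this direction. For the year-1 DID in the three fading patterns, the ratios are √(0.583/0.55) = 1.03, √(0.517/0.45) = 1.07 and √(0.450/0.35) = 1.13, so that standard error would be too large.

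**The case against.** The strongest reply is that neither condition is in the article. It never calls the random effects intercepts. A participant intercept is written out only in the linear model that introduces the repeated cross-section fallback. With z_ht changing over time, the formula does allow the covariance to differ between pairs of years. This stands as far as it goes: constant correlation is not forced everywhere. It helps little in the five control parks, where z_ht is expected to change little. In restored parks it ties the covariance to the state of the park and not to elapsed time.

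Second, a condensed article may leave the residual covariance type and the SE estimator to an analysis plan that is not shown. An empirical standard error or a residual structure there could remove the problem. That is fair, and silence on those details is not the point. The point is the form that the article does state, with one set of random effects on park features serving two purposes.

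Third, fading correlation is assumed. This stands in full. A reader might infer that the false-positive rate of this plan exceeds 5%. The documents do not support that, because they give only a lower bound for r and nothing by interval. Under constant correlation the error rate is 5%.

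A reader might also take the single r in the Sample size section as the same mistake. It is not, since that calculation concerns one baseline-to-year-3 contrast.

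Finally, the general promise of robustness checks could cover this issue, but it names no covariance check and leaves the main test as it is.

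**Conclusion.** The point holds conditionally. As written, the model is a poor device for serial correlation. If it is fitted with participant intercepts, or if z_ht is close to constant, and model-based standard errors are used, the year-3 DID is exposed to any fading of the correlation. With 0.35 at three years and 0.45 to 0.65 at one year, the standard error is about 95% to 83% of its true value, and the nominal 5% test rejects about 6% to 10% of the time. The lower end of the range is no inflation at all, when correlation is constant. These figures rest on assumed decay patterns, equal variances over visits and no park effect. They concern within-person covariance only and are separate from the question of how nine parks are handled. An error in the planned standard error is not demonstrated. The change is nonetheless worth making, because it removes the dependence on an untested assumption at almost no cost.

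**What to change.** In the Statistical analysis section, for the continuous outcomes, replace the random effects on z_ht with an unstructured 4×4 covariance over the four visits within participant (in SAS, a REPEATED statement on visit with the participant as subject and TYPE=UN). Model park clustering with separate park-level terms, so that each source of correlation has its own part of the model.

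This changes the analysis wording only. An unstructured covariance has 4 × 5/2 = 10 parameters against 2 for a random intercept with residual error, estimated from 620 participants at baseline and about 450 at year 3. It remains valid if the correlation turns out to be constant. The price is the eight extra parameters and possibly a slightly wider interval for the year-3 contrast. The Sample size section can stay as it is on this point.
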